**Methods:**

This study is a double-blinded randomized controlled trial. Samples will be divided into three groups, and 500 mg vitamin C three times daily (1500 mg/day), or placebo will be received for seven weeks. Clinical characteristics, ascorbic acid, malondialdehyde, and total antioxidant capacity of patients in serum and aqueous humor will be measured before and after intervention and phacoemulsification.

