### Aims

The aim of this study is to analyze the protective effect of oral ascorbic acid supplementation on corneal endothelial cells which undergo oxidative stress due to phacoemulsification in patients with hard nucleus cataracts. The primary outcome will investigate mean change and percentage in endothelial cell density (ECD) loss prior to and after phacoemulsification, assessed at postoperative follow-up period (day 1, week 1, week 4, and week 6) of patients with hard nucleus cataracts.

The secondary endpoint will investigate mean change in other clinical parameters such as central corneal thickness (CCT), visual acuity, and cells in the anterior chamber during the postoperative follow-up period. This study will investigate differences in MDA levels in aqueous humor, prior to and after phacoemulsification, and compare between groups with vitamin C supplementation and those without. We will also investigate differences in AA, TAC, and MDA levels in serum and aqueous humor at the start of the study and after seven days of supplementation and compare them between the three groups. Furthermore, we will explore the correlation between aqueous humor and serum AA, TAC, and MDA levels.

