### Screening

We screen patients who sign up for a mass cataract surgery event in a regional hospital in Cianjur, West Java, Indonesia. Patients will be asked for information regarding personal identification, history of systemic and ocular diseases, and allergies. They then will undergo ophthalmology examination including uncorrected visual acuity (UCVA) and best corrected visual acuity (BCVA), intraocular pressure using non-contact tonometry (NCT), biomicroscopy slit lamp, and indirect fundoscopy to evaluate anterior and posterior chambers. Lens opacity will then be measured using LOCS III criteria. We will also examine ECD, coefficient of variety (COV), and hexagonality of endothelial cell layers using a specular microscope (REM 4000, Rodenstock, Germany), central corneal thickness (CCT) using Anterior Segment Optical Coherence Tomography (ASOCT), and biometry. Blood samples will be then drawn from patients to measure serum AA, MDA, and TAC.

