### Intervention

Patients will be divided into three groups, each with 40 samples. The first group (n=40) will receive 500 mg oral vitamin C three times daily (1500 mg/day) for one week before surgery to four weeks after surgery. The second group (n=40) will receive 500 mg oral vitamin C three times daily (1500 mg/day) for one week before surgery and a placebo after surgery. The last group (n=40) will receive a placebo one week before surgery to four weeks after surgery. Oral vitamin C 1500 mg/day was chosen based on pharmacokinetic evidence showing that this dosage can achieve stable plasma concentrations and approach a steady-state level during short-term administration.
^
15
^

To minimize potential bias related to surgical variability, all phacoemulsification procedures will be performed using standardized surgical techniques. The surgeries will be conducted by experienced cataract surgeons using the same phacoemulsification machine and standardized operative settings. Key intraoperative parameters, including ultrasound power, irrigation parameters, and the type of ophthalmic viscosurgical device (OVD), will be standardized across all procedures.

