### Post-intervention evaluation

Patients will be asked to come a week after screening. Firstly, they asked the side effects of the supplementation, including gastrointestinal disorders (nausea, diarrhea, epigastric pain). Second blood samples will be then drawn to measure post-intervention serum AA, MDA, and TAC.

Sampling for oxidative stress in the aqueous humour will be performed twice, pre- and post-phacoemulsification. During surgery, after the initial incision, 0.2 mL of aqueous humor will be taken using a 1 cc syringe with a 30 G cannula. Phacoemulsification will then be conducted using standard operating procedure to intraocular lens implantation. Another 0.2 mL of aqueous humor will then be taken three minutes after removing the viscoelastic as a post-phacoemulsification sample. This sampling volume is within the range commonly used in aqueous humor biomarker studies and is considered safe under surgical conditions. Because the sampling will be performed through the surgical incision and the anterior chamber will subsequently be maintained with a balanced salt solution, anterior chamber stability will not be affected.
^
16,
17
^ The pre-phacoemulsification aqueous humour samples will be analysed for ascorbic acid (AA), total antioxidant capacity (TAC), and malondialdehyde (MDA), while the post-phacoemulsification samples will be analysed for MDA levels only. Intraoperative parameters, including effective phacoemulsification time (EPT) and total surgical duration, will be recorded for each procedure. All patients will receive topical medications: levofloxacin 5 mg/mL every three hours for one week, prednisolone acetate 10 mg/mL every three hours for 1 week, and tapered down in 4-6 weeks.

Every patient will be evaluated one day, one week, four weeks, and six weeks post-phacoemulsification to measure study parameters and signs of complications, i.e. inflammation or infection. Patients who experience side effects or complications, including toxic anterior segment syndrome (TASS) or endophthalmitis during the duration of follow-up will be exempted from the study and managed according to the standard operational procedure of the Department of Ophthalmology, Faculty of Medicine, University of Indonesia.

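### The Aims call for aqueous humour markers at the start of the study, but aqueous humour is first sampled at surgery, after the week of capsules, so no aqueous change with supplementation can be computed

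*Protocol article*

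**What the plan says.** **Objective.** The Aims section plans to examine differences in AA, TAC and MDA "levels in serum and aqueous humor at the start of the study and after seven days of supplementation" and to compare them across the three groups. The Methods part of the abstract says of the same markers that they "in serum and aqueous humor will be measured before and after intervention and phacoemulsification".

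**Collection at the start.** Under Screening, the only biological sample is blood: "Blood samples will be then drawn from patients to measure serum AA, MDA, and TAC".

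**Treatment before surgery.** Under Intervention, all three groups take capsules in the week before the operation. The first group, for example, receives vitamin C "for one week before surgery to four weeks after surgery".

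**Aqueous collection.** Under Post-intervention evaluation, "Sampling for oxidative stress in the aqueous humour will be performed twice, pre- and post-phacoemulsification". The first sample is intraoperative: "During surgery, after the initial incision, 0.2 mL of aqueous humor will be taken using a 1 cc syringe with a 30 G cannula". The second follows three minutes after the viscoelastic has been removed. The first sample is assayed for all three markers, "while the post-phacoemulsification samples will be analysed for MDA levels only". The Laboratory analysis section gives the same two aqueous time points and adds a second blood sample after seven days of supplementation.

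**The concern.** The objective attaches two fluids to two times, and the sampling schedule supplies one of those fluids at only one of those times. This is not a detail that an article leaves to a fuller document. The article states the objective and also states a schedule that cannot deliver part of it, and no analysis plan can supply a sample that was not taken.

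The affected part matters for interpretation. The Introduction hypothesises that oral vitamin C raises AA and antioxidant capacity in the aqueous humour, and the aqueous comparison is the direct test of that step. With the samples described, the evidence will be a randomised comparison of on-treatment levels. That is sound evidence, but it does not show that levels rose within patients. A report that follows the wording of the Aims would promise such a rise without the data for it.

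**Working it through.** No sample-size or power figure bears on this point, so there is no plan figure to reproduce. The check sets the times that the objective needs against the samples that the schedule provides.

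Inputs: the objective (Aims; abstract), the start-of-study sample (Screening), the pre-surgical treatment week (Intervention), and the timing and assays of later samples (Post-intervention evaluation; Laboratory analysis).

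| Marker and fluid | Start of study | After seven days, before phacoemulsification | After phacoemulsification | Change over supplementation |
|---|---|---|---|---|
| Serum AA, TAC, MDA | yes (screening blood) | yes (second blood sample) | not planned | computable |
| Aqueous AA, TAC | no | yes (after incision) | not assayed | not computable |
| Aqueous MDA | no | yes (after incision) | yes | not computable |

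Counting the cells that the objective needs:

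- Required: 2 fluids × 3 markers × 2 times = 12.
- Supplied: serum 3 × 2 = 6, plus aqueous 3 × 1 = 3, giving 9.
- Missing: 12 − 9 = 3, namely aqueous AA, TAC and MDA at the start of the study.
- Changes over supplementation that can be computed: 3 of 3 in serum and 0 of 3 in aqueous humour.

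The gap is structural. It applies to all 3 × 40 = 120 planned patients and has nothing to do with missing data.

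The pre-phacoemulsification sample cannot fill the missing cells. It precedes the ultrasound but follows a week of capsules, so it is a baseline for surgery and not for treatment.

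Three analyses are untouched by the gap: the comparison of aqueous AA, TAC and MDA between randomised groups in the pre-phacoemulsification sample; the aqueous MDA change from before to after phacoemulsification; and the correlation of aqueous with serum levels after seven days.

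**The case against.** **The sentence may be shorthand.** It could be meant as serum at both times and aqueous humour after seven days only. That reading fits the schedule and may well be the intention. But the sentence joins both fluids to both times, and the abstract repeats the before-and-after wording for both. The restriction has to be written down.

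**The objective is largely intact.** This stands. A reader might infer that the whole secondary objective cannot be computed. It can, apart from the aqueous values at study start. Because allocation is randomised and there is a placebo group, the comparison of aqueous levels after seven days is valid without an aqueous baseline.

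**The abstract should not be read as an endpoint list.** This also stands. A reader might infer that AA and TAC endpoints across phacoemulsification were promised and are missing, since the second aqueous sample is assayed for MDA only. That inference rests on one compressed sentence covering several measurements, two fluids and two events. The Aims limit the comparison across phacoemulsification to MDA, and Post-intervention evaluation agrees. There is no contradiction between Aims and Methods there.

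**No misuse of the first aqueous sample is planned.** This stands too. A reader might fear that it will be treated as an untreated baseline and adjusted for, which would remove part or all of the supplementation effect. No section calls it a treatment baseline or proposes that adjustment. The Statistical analysis section plans one-way ANOVA or Kruskal–Wallis across groups, and the covariates it names are phacoemulsification time, surgical duration, smoking, occupational and ultraviolet exposure, and dietary vitamin C. Explicit labelling is a precaution, not the correction of a planned error.

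**Conclusion.** The contradiction is certain on the text: the Aims require aqueous AA, TAC and MDA at the start of the study, and the schedule provides no aqueous sample before supplementation. Three of the twelve fluid-by-marker-by-time values named by the objective are unobtainable, and with them all three aqueous changes over supplementation, in every group. The conclusion assumes that the sampling described is complete. Two sections agree on the two intraoperative samples, and none mentions another.

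The reach is limited. This is one component of a secondary objective. The primary endothelial cell density outcome, the serum changes, the aqueous group comparison after seven days and the aqueous MDA change across surgery are unaffected. The documents do not support going further, to a non-computable objective, lost AA and TAC surgical endpoints or a planned over-adjustment. The wording should still be corrected, because it determines what the trial may claim about aqueous antioxidant levels.

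**What to change.** In the Aims:

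- Limit the comparison of study start with day 7 to serum AA, TAC and MDA. Analyse the day-7 value adjusted for the pre-treatment value already collected. The contradiction does not force this adjustment, but it uses existing data and settles how the serum comparison is made.
- Define the aqueous AA, TAC and MDA endpoint as a between-group comparison of the single pre-phacoemulsification sample. Label it as taken after supplementation, and state that it is not a treatment baseline.
- Leave the aqueous MDA comparison across phacoemulsification as it is.

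In the abstract, align the wording so that measurement before and after the intervention refers to serum.

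The cost is wording only: no new samples, no change to treatment and no effect on sample size. The Study status section places the trial in data processing at submission, so the definition can be changed but presumably not the sampling. The change should be dated and disclosed. The downside is the weaker aqueous claim: a difference in level between groups instead of a change within patients.

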### Randomization, blinding and allocation concealment

The subjects will be allocated into three groups: Group 1 will receive oral vitamin C 500 mg, three times daily pre- and postoperatively, Group 2 will receive it only preoperatively, and Group 3 will receive a placebo. Participants will be randomly assigned to the study groups using a computer-generated block randomization sequence with a block size of four. The randomization sequence will be prepared by an independent researcher who will not be involved in patient recruitment or outcome assessment. Allocation concealment will be ensured using sequentially numbered, sealed, opaque envelopes. The study will be conducted in a double-blinded manner. Operating surgeons, examiners, laboratory analysts, and study participants will be blinded to group allocation throughout the study period. Participants will be followed up for seven weeks, and data will be analyzed after the minimum required number of participants has been reached.
Figure 1 shows the planned CONSORT flow diagram of participants screening, randomization, follow-up, and analysis.

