### Laboratory analysis

The examination of blood and aqueous humor samples will be conducted at the Pharmacology Laboratory, Faculty of Medicine, Universitas Indonesia (FMUI). Blood samples will be collected from all study participants who will have provided written informed consent. The collection, storage, and transportation procedures will be carried out under strict control of time and temperature to maintain sample stability. All participants will be gathered at the same time, and blood samples will be collected sequentially within a short period so that the entire process, from the first to the last sample, will be completed within one hour.

Immediately after collection, blood samples will be temporarily stored in a cooler box and will be transported from Sayang General Hospital, Cianjur, to the Pharmacology Laboratory, FMUI, under police escort from the Cianjur Police Department. The total transport time will be less than two hours. Centrifugation will be performed within six hours after collection at a speed of 1,000G for 15 minutes to obtain plasma, will be then stored at −80°C until further analysis.

Participants will be randomly assigned into three groups using computer-generated randomization: one placebo group and two intervention groups receiving oral vitamin C supplementation at predetermined doses. Each participant will be provided with a logbook containing the follow-up schedule, adverse effect monitoring, and contact information in case of any complaints. A second blood sample will be collected after seven days of supplementation for the analysis of ascorbic acid (AA), total antioxidant capacity (TAC), and malondialdehyde (MDA).

Aqueous humor samples will be collected twice, each of 0.2 mL: first, immediately after the incision (pre-phacoemulsification), and second, three minutes after viscoelastic removal following intraocular lens implantation (post-phacoemulsification). Both aqueous humor samples will be stored in a cool box containing dry ice at −78°C and will subsequently be transferred to long-term storage at −80°C in the Pharmacology Laboratory, FMUI, before analysis.

Principles of Analysis:
1.Measurement of Ascorbic Acid (AA) Levels
Ascorbic acid levels will be determined using an Enzyme-Linked Immunosorbent Assay (ELISA) Kit for Vitamin C (Cat. No. CEA913Ge). The principle of this assay is based on a competitive inhibition enzyme immunoassay method.2.Measurement of Total Antioxidant Capacity (TAC)

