### Statistical analysis

Data from this study will be recorded and analyzed by IBM SPSS 20.0. Sample personal identification, including demographic and clinical characteristics, will be reported in a descriptive analysis. Data distribution of numerical variables will be assessed using the Shapiro–Wilk test with normal distribution will be presented as mean (standard deviation [SD]); non-normal distribution will be reported as median (interquartile range [IQR]). Nominal data will be reported in frequency and percentage. We will use Pearson’s chi-squared test for categorical data. For comparisons among the three groups, one-way ANOVA will be used for normally distributed data, while the Kruskal–Wallis test will be used for non-normally distributed data. Significant group differences will be followed by post-hoc pairwise comparisons using Bonferroni correction for ANOVA or Dunn’s test following the Kruskal–Wallis analysis to account for multiple testing. Pearson’s test will be used to test the correlation between data in aqueous humor and serum. A p-value of less than 0.05 (p < 0.05) will be considered statistically significant.

Effective phacoemulsification time (EPT) and total surgical duration will be included as covariates in the statistical analysis to account for their potential influence on postoperative endothelial outcomes. Multivariable analysis will also be conducted to control for potential confounding variables, including smoking status, occupational exposure, ultraviolet (UV) light exposure, and dietary intake of vitamin C. These variables will be collected through structured questionnaires during the screening.

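### Serum and aqueous biomarkers are compared across three groups although the two vitamin C arms are treated alike until surgery: valid, but less powerful than pooling those arms

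*Protocol article*

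**What the plan says.** **Regimens.** Under Intervention, Group 1 takes "500 mg oral vitamin C three times daily (1500 mg/day) for one week before surgery to four weeks after surgery". Group 2 takes the same daily amount "for one week before surgery and a placebo after surgery". Group 3 takes placebo throughout. The Randomization section agrees: "Group 2 will receive it only preoperatively".

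**Timing of samples.** Laboratory analysis states: "A second blood sample will be collected after seven days of supplementation". Post-intervention evaluation places both aqueous samples within the operation. The first, taken after the incision, is assayed for AA, TAC and MDA. The second, taken three minutes after viscoelastic removal, is assayed for MDA only. No later biomarker sample is planned.

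**Comparisons.** The Aims compare serum and aqueous AA, TAC and MDA at the start and "after seven days of supplementation and compare them between the three groups". The sentence before that concerns aqueous MDA before and after phacoemulsification, which the plan will "compare between groups with vitamin C supplementation and those without".

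**Tests.** Statistical analysis states: "For comparisons among the three groups, one-way ANOVA will be used for normally distributed data". Kruskal–Wallis replaces ANOVA for non-normal data. If the result is significant, pairwise tests follow, with Bonferroni correction or by Dunn's test. No two-group test for numerical data is named.

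**The concern.** The Introduction hypothesises that oral vitamin C raises AA and antioxidant capacity in the aqueous humor. For samples taken by the end of surgery, that is a question about supplemented versus unsupplemented participants. Two of the three arms are then one and the same treatment condition.

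A three-group test spends one of its two degrees of freedom on Group 1 versus Group 2, where no treatment effect can exist. The pairwise tests that follow split the supplemented participants into two halves, each compared with placebo at a stricter level. At stake is some power for the mechanistic outcomes. There is also a risk of awkward results, such as one of two identically treated arms being declared different from placebo and the other not.

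**Working it through.** **1. When the arms diverge.** Groups 1 and 2 have the same regimen up to surgery and differ only afterwards. Day-7 serum, pre-phacoemulsification aqueous humor and post-phacoemulsification aqueous humor are all collected before any postoperative dosing. On all of them the expected means can be written (d, d, 0), in SD units relative to Group 3.

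**2. The plan's own sample size.** Sample size calculation gives SD 201, difference 132, α 0.05 and power 80%. Then n = 2 × [201 × (1.960 + 0.842) / 132]² = 36.4 per group. The plan states 36 (power 79.6% at 36), and 36 / 0.9 = 40 after the 10% allowance. The figure is reproduced, to rounding, as an unadjusted two-arm comparison of endothelial cell density (ECD) loss. It says nothing about biomarkers.

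**3. Inputs for the biomarkers.** The protocol gives no biomarker SD or effect. I assume d from 0.3 to 1.0, including 132/201 = 0.657 borrowed from the ECD calculation. I take n = 36 per group (40 as a check), normal data and two-sided tests.

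**4. Formulas, n = 36.**
- Three-group ANOVA at 0.05: the squared deviations of (d, d, 0) from their mean sum to (2/3)d², so the noncentrality is λ = 36 × (2/3)d² = 24d², on 2 and 105 degrees of freedom.
- Pooled contrast, 72 v 36, at 0.05: δ = d / √(1/72 + 1/36) = d√24, so δ² = 24d², on 106 degrees of freedom.
- One Bonferroni pair, 36 v 36, at 0.05/3: δ = d / √(2/36) = d√18, on 105 degrees of freedom.

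ANOVA and the pooled contrast carry the same noncentrality. ANOVA spreads it over two numerator degrees of freedom instead of one, and that is the whole of the loss.

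**5. Power, 36 per group.**

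| d (SD) | ANOVA | Pooled | Loss, ANOVA v pooled | One Bonferroni pair |
|---|---|---|---|---|
| 0.3 | 23.5% | 30.8% | 7.3 | 12.8% |
| 0.4 | 39.1% | 49.3% | 10.2 | 23.6% |
| 0.5 | 57.1% | 68.0% | 10.9 | 38.1% |
| 0.657 | 81.8% | 89.0% | 7.2 | 63.8% |
| 0.8 | 94.3% | 97.3% | 3.0 | 83.0% |
| 1.0 | 99.4% | 99.8% | 0.4 | 96.3% |

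With a variance from the two arms only (70 degrees of freedom), the single pair has 37.6% power at 0.5 SD and 63.2% at 0.657 SD.

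At 40 per group, ANOVA v pooled is 62.1% v 72.6% at 0.5 SD and 85.9% v 92.0% at 0.657 SD.

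**6. Difference detectable with 80% power, 36 per group.** Pooled 0.577 SD, ANOVA 0.643 SD, one Bonferroni pair 0.773 SD.

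**7. The planned sequence.** I simulated ANOVA followed, if significant, by Bonferroni pairs (40,000 runs, d = 0.657, 36 per group). At least one vitamin C arm differs from placebo in 78.8% of runs, and both do in 48.5%. A false Group 1 versus Group 2 finding occurs in 1.7%.

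**The case against.** **The first test is the omnibus at 0.05.** It is tempting to say that the question is tested with 36 versus 36 at 0.0167, and so to quote 38% against 68%. The plan does not support that as the headline. The pairs come second, and when only Group 3 differs the omnibus test itself bears on whether vitamin C matters. The fair comparison is ANOVA against pooled; the single-pair figures describe only the follow-up step. This stands.

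**The loss may be trivial.** With no biomarker effect in the protocol, a large true effect is possible, and at 1.0 SD the loss is 0.4 points. Also, 36 per group assumes the full 10% loss, although these samples precede postoperative follow-up. Both points stand, and only a range can be given.

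**The Aims do not contradict themselves.** A reader might infer that they do, because one sentence uses with versus without supplementation and the next uses three groups. The sentences concern different quantities: aqueous MDA around phacoemulsification, and the levels at the start and after seven days. Different comparisons for different quantities are not a contradiction. The first sentence already has the pooled contrast in substance; what it lacks is a matching test in Statistical analysis.

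**A spurious Group 1 versus Group 2 result is rare.** The omnibus gate and Bonferroni hold it to 1.7% per outcome in the simulation, so the planned test cannot be called invalid. It is also too strong to say that the analysed groups could differ only by chance. Participants may be removed for missed follow-up, low intake, side effects or complications, some of this after the arms diverge, so selection could separate those retained. That would be an artefact and not a treatment effect.

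**Doses.** Laboratory analysis speaks of predetermined doses for the two intervention groups. This does not imply different preoperative doses, since Intervention states the same one for both.

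**Conclusion.** The point holds as one of efficiency. On day-7 serum and intraoperative aqueous biomarkers no treatment effect can distinguish Group 1 from Group 2, yet the plan states a three-group comparison for the seven-day levels and names no other between-group test for numerical data. Against a pooled contrast, the omnibus test loses about 7 to 11 points of power for assumed effects of 0.3 to 0.657 SD, about 3 points at 0.8 SD and under 1 point at 1.0 SD, with 36 per group. A single Bonferroni pair against placebo loses more: about 30 points at 0.5 SD and 25 at 0.657 SD. These figures rest on assumed effect sizes, normal data and equal effects in the two vitamin C arms before surgery; the last follows from the design.

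It would be wrong to infer that the trial's main result is at risk. These are not primary outcomes, type I error is not inflated by the three-group test, and the ECD outcome and its sample size are untouched.

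**What to change.** - For day-7 serum AA, TAC and MDA and for pre-phacoemulsification aqueous AA, TAC and MDA, make Groups 1+2 combined versus Group 3, at two-sided 0.05, the main comparison.
- In Statistical analysis, name the two-group test (for example a two-sample t-test, or Mann–Whitney where the data are not normal). State that it also serves the aqueous MDA comparison around phacoemulsification, which the Aims already word as with versus without supplementation.
- Keep the three-group comparison for postoperative outcomes, where the arms do differ.

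The cost is a sentence or two and no new data. There is a small downside. Study status puts the trial in data processing in September 2025, so this is a late change. It should be dated and disclosed, and labelled post hoc if anyone involved has seen group-level results.
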